### 2.14. Data management and protection

Most data, including the usage data on the App, will be documented during visits by the research assistant at each participating hospital; the original forms will be stored in a closed cabinet. Additionally, all unidentifiable data will be saved in a Dropbox-based central data management system^2^ weekly. Identifying information will be kept only in a local database isolated from the external network with restricted access. Since the central data management system is mirrored, data confidentiality and accessibility are always guaranteed. The permission to access data will be managed by the study coordinator. We will conduct self-inspection on consent forms and case records through weekly research meetings.

If a patient withdraws their participation in part or full, it will be recorded in the records, and no additional data (as determined by the patient) will be added. The patient’s data will not be used in the analysis and, if desired, will be removed from the project database (only data already used in studies and project outcomes will be excluded). After the data collection is complete, all identifying variables will be physically removed from the rest of the data. The analysis will be carried out in a purely pseudonymous way.

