#### 2.7.2. Usual treatment for depression

All participating patients will continue all of their usual treatments for depression during the research period. To minimize the confounding effect of medication, the use of new psychiatric medications, including antidepressants and benzodiazepines, will be limited. The use of zolpidem and zopiclone for insomnia is possible. To participate in the study, a stable dosing period of 4 weeks is required, so considering the course of psychiatric drug treatment, in general, the possibility of changing medication will not be high. However, psychiatrists will address any changes in depression symptoms of participants immediately after they are identified. Should there be medication changes, participants’ will be entitled to withdraw from the study, and our research team will assess their situation to see if they need another treatment.

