### 2.12. Sample size and power calculations

To the best of our knowledge, there are no studies on stress-reduction programs for depression patients using a mobile application; hence, we have assumed the sample size based on the effect size of 0.28, being half of the effect size of 0.56 reported in a previous study that applied MBSR in patients with depression (59). For all patients with depression, the change in DASS-21 score from pre- to post-administration of the App would be analyzed using analysis of variance for a 2 × 2 crossover design (60). As we have assumed no carry-over effects, this was not considered in calculating the sample size. Sample size calculations were conducted using the statistical software G * Power 3.1.9.2 (61). The minimum sample was identified as 172 (fAPP = 86, dAPP = 86) based on an estimated between-group effect on post-intervention stress outcomes between the fAPP and dAPP with a power of 0.95 and an alpha of 0.05. Therefore, the current study will enroll 215 participants and allow for up to a 20% loss to follow-up, expecting a minimum effective sample size of 172 individuals.

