### 2.13. Data analyses

Data analysis will adhere to CONSORT rules (62), i.e., primarily on an intention-to-treat basis. The pre-randomization scores in the two conditions prior to receiving the intervention will be compared to ensure absence of significant differences between them on the outcome measures. Then, a multilevel linear mixed model will be computed, successfully managing missing data. The first evaluation of participants with missing data will assume that data are missing at random in the linear mixed model. Multiple imputation, last observation carried forward imputation, and assessment of the per protocol completers will be used to assess the sensitivity of this assumption, which should minimize the number of missing data. All measurement items will be incorporated into the model. The parameters will be estimated using a restricted maximum likelihood approach. If baseline differences are found, they will be included as variables in the linear mixed model. All analyses will be performed with SPSS v26.0.

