### 2.15. Ethical approval

All procedures conducted during this trial with human participants will be carried out in compliance with institutional ethical standards. All research procedures have been approved by an Institutional Review Board (IRB) at each participating site: Korea University Guro Hospital (IRB Reference No. 2021GR0585), Korea University Anam Hospital (IRB Reference No.2021AN0596), and Korea University Anam Hospital (IRB Reference No. 2021AS0391). This protocol has been prepared in accordance with the SPIRIT 2013 statement (63). The study was registered under ClinicalTrials.gov 2021GR0585 on 31 March 2022 and will be conducted following the CONSORT guidelines (62).

Participation will be voluntary and based on informed consent. All eligible participants will be given oral and written information about the study. Specifically, they will be informed that they may leave the study at any time, without providing any explanation, and that this decision will in no way affect their regular treatment at the center. The treatments will be carried out by qualified and expert professionals. In addition, according to the existing knowledge in this field, we have not found any potential risks for the participants; however, the appearance of any important clinical change involving any type of risk would not only imply removal of the participant from the project, but also their referral for specialized study and care.

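### Section 2.14 drops all data of any participant who withdraws, partly or wholly, which contradicts the intention-to-treat mixed model in section 2.13 and can bias the App effect

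*Protocol article*

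**What the plan says.** Section 2.14 (Data management and protection) sets the trigger: "If a patient withdraws their participation in part or full, it will be recorded in the records". Nothing further is then collected, to the extent that the patient decides, and the patient's "data will not be used in the analysis and, if desired, will be removed from the project database". A parenthesis follows: "only data already used in studies and project outcomes will be excluded". Its meaning is unclear. It appears to limit what can be erased, and it does not put the data back into the analysis.

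Section 2.13 (Data analyses) says that the analysis is "primarily on an intention-to-treat basis". On dropout it says: "The first evaluation of participants with missing data will assume that data are missing at random in the linear mixed model". Per-protocol completers, last observation carried forward and multiple imputation appear there only as sensitivity checks.

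Three other sections bear on this:

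- Section 2.7.1 says that failing to follow the usage guideline does not decide whether a participant's data are excluded.
- Section 2.7.2 says that participants whose medication changes are "entitled to withdraw from the study, and our research team will assess their situation".
- Section 2.15 says that an important clinical change involving risk "would not only imply removal of the participant from the project".

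Section 2.12 enrols 215 to "allow for up to a 20% loss to follow-up", leaving 172.

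**The concern.** A likelihood-based mixed model deals with dropout by using what was observed before the participant left. Under missing at random, the V0 and V1 scores of someone who leaves after V1 carry the information about the missing V2. If those scores are discarded, the participant leaves the analysis altogether, and for withdrawers the comparison rests only on those who stayed. That is a selection made after randomisation.

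It does harm when leaving is related to how the participant is doing and when that relation differs between the groups. Both are plausible here. Section 2.7.2 ties the option to withdraw to a medication change. Participants know their allocation (section 2.1). The KRW 100,000 reward depends on completing the four-week App period (section 2.4), which ends at week 4 for the App-first group and at week 8 for the wait-list group. An App-first participant who withdraws in the second period would also lose a complete first-period record (V0 to V2), which bears directly on the primary hypothesis.

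Two analysts, one following section 2.13 and the other section 2.14, would analyse different people and could report different effects.

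**Working it through.** **1. Reading the rule.** Section 2.14 contains three separate steps: no further data (as the patient decides), no use in the analysis (no condition), and removal from the database (if the patient wishes). The middle step does not depend on any request. It is therefore more than a clause that honours erasure requests.

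**2. Side by side with the analysis.** Section 2.13 keeps everyone randomised, with observed scores in the model. Section 2.14 removes withdrawers and their observed scores. Section 2.13 treats completers as a sensitivity set; for withdrawers, section 2.14 applies that restriction to the primary analysis. Section 2.7.1 keeps the data of those who do not use the App as advised. Yet someone who says they are stopping the App but still attends visits might count as a partial withdrawal under section 2.14. The article does not draw that line.

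**3. How many.** The enrolment figure reproduces: 172 / (1 − 0.20) = 215. The allowance is 215 − 172 = 43, and 43 / 215 = 20%. This is an upper bound within the plan's own allowance, because that allowance is for loss to follow-up and the share that is formal withdrawal is not given. The plan already expects 172 to remain, so within that allowance the problem is bias and an inconsistent analysis set, not sample size.

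**4. How much bias is possible.** The documents give no withdrawal rates by group, no correlation between visits and no link between withdrawal and outcome. All of these are assumed below, and only the first period (V0, V1, V2) is modelled.

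*Set A.* Assumptions: 108 per arm (215 / 2 = 107.5); unit-variance scores with correlation 0.6; App effect 0.14 SD at V1 and 0.28 SD at V2; withdrawal after V1; 4,000 runs; Monte Carlo standard error 0.002. Where withdrawal depends on V1, logit P = a + 1.2 × V1, an odds ratio of exp(1.2) = 3.3 per SD. The exclusion estimate is the unadjusted difference in mean V2 among those who stayed. The missing-at-random estimate regresses V2 on V0 and V1 within each arm among those who stayed and averages the predictions over everyone in the arm. Effects are in SD in favour of the App:

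| Withdrawal (wait-list / App) | Full data | Observed data kept | Withdrawers dropped | Shift (dropped − full) |
|---|---|---|---|---|
| Random (20% / 20%) | 0.277 | 0.277 | 0.277 | 0.000 |
| Same V1-dependence in both arms (21% / 19%) | 0.285 | 0.285 | 0.271 | −0.014 |
| V1-dependent in App arm only (20% / 22%) | 0.282 | 0.281 | 0.407 | +0.125 |
| V1-dependent in App arm only, unequal rates (10% / 29%) | 0.277 | 0.276 | 0.441 | +0.164 |

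*Set B.* Same arm size, correlation and true effect, about 20% withdrawing, but with V2 adjusted for V0 by ANCOVA and withdrawal odds rising 2.7- to 4.5-fold per SD of worsening at V1 in one arm only. Dropping withdrawers gives 0.33 to 0.35 if this happens in the App arm (shift +0.05 to +0.07) and 0.23 to 0.21 if in the wait-list arm (shift −0.05 to −0.07). A true effect of zero becomes about 0.05 to 0.08. Keeping V0 and V1 returns 0.28.

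Set A shows larger shifts mainly because it does not adjust for baseline; adjustment absorbs part of the selection. In both sets withdrawal depends only on scores already observed, so the missing-at-random estimate is right by construction. The sets show what is lost by discarding those scores. They do not show that missing at random holds in this trial.

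**The case against.** The strongest reply is that section 2.14 is a data-protection paragraph, loosely condensed and partly garbled, that section 2.13 is the section governing the analysis, and that the team may well intend to follow section 2.13. That is possible. It does not remove the conflict, because section 2.14 speaks expressly of use in the analysis and attaches no condition.

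Several stronger readings are tempting, and the document does not support them:

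- **That the primary analysis becomes a completers analysis with nothing left to model.** The rule applies to withdrawal only. Participants who miss visits or are lost without withdrawing stay in the mixed model and in the imputation.
- **That 43 participants will be dropped.** That figure takes a loss-to-follow-up allowance as if all of it were formal withdrawal.
- **That those dropped are known to be selected on outcome.** Section 2.7.2 only entitles participants to withdraw, and it expects medication changes to be uncommon. Section 2.15 describes removal by the team and does not say that the data of those removed are discarded.
- **That the effect will be biased, in a given direction.** With random withdrawal, or the same mechanism in both groups, the simulated shift is between 0 and about 0.01 SD. No passage establishes a difference between the groups; it is plausible, not shown.

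The reply is also right that the simulations rest on invented inputs and model one period of an eight-week crossover. They show that bias is possible and do not estimate it for this trial.

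**Conclusion.** The contradiction between sections 2.13 and 2.14 is real and stands on the wording alone. It is a wrongly stated rule, not detail left to an analysis plan, and it decides who enters the primary analysis. Followed literally, section 2.14 discards observed post-randomisation scores and can bias the App effect.

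The size and direction are unknown. Under the assumed inputs, the shift on a true 0.28 SD runs from about 0 to about 0.05–0.16 SD. The upper part of that range requires outcome-related withdrawal in one group only and no baseline adjustment. The group affected determines the sign. The number affected is at most 43 of 215 within the planned allowance, and probably fewer, since not every loss is a formal withdrawal.

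**What to change.** Replace the sentence in section 2.14 with wording such as: *Data collected up to withdrawal are retained in the intention-to-treat analysis unless the participant withdraws consent to their use; such cases are counted and reported by group.*

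Distinguish stopping the App from stopping assessments, so that a participant who gives up the App but still attends visits keeps contributing data, in line with section 2.7.1. Clarify or delete the parenthesis on data already used.

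Reconcile sections 2.7.2, 2.14 and 2.15 on one further point: whether the data of participants whom the team removes are kept. This concerns only the use of data already collected. The clinical rule on removal and referral is not at issue and need not change.

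The cost is a wording change to the protocol and the matching consent text (the consent form is not shown here), with review-board approval. Participants keep the right to have their data erased. The change should be made before outcome data are examined, so that the choice of analysis set cannot depend on the results.

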### 2.15. Ethical approval

All procedures conducted during this trial with human participants will be carried out in compliance with institutional ethical standards. All research procedures have been approved by an Institutional Review Board (IRB) at each participating site: Korea University Guro Hospital (IRB Reference No. 2021GR0585), Korea University Anam Hospital (IRB Reference No.2021AN0596), and Korea University Anam Hospital (IRB Reference No. 2021AS0391). This protocol has been prepared in accordance with the SPIRIT 2013 statement (63). The study was registered under ClinicalTrials.gov 2021GR0585 on 31 March 2022 and will be conducted following the CONSORT guidelines (62).

Participation will be voluntary and based on informed consent. All eligible participants will be given oral and written information about the study. Specifically, they will be informed that they may leave the study at any time, without providing any explanation, and that this decision will in no way affect their regular treatment at the center. The treatments will be carried out by qualified and expert professionals. In addition, according to the existing knowledge in this field, we have not found any potential risks for the participants; however, the appearance of any important clinical change involving any type of risk would not only imply removal of the participant from the project, but also their referral for specialized study and care.

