## 2. Materials and methods

### 2.1. Design

This study is a single blind, multicenter, randomized, controlled crossover trial (Figure 1). All subjects who meet the inclusion and exclusion criteria will be randomly assigned to the App first group (fAPP) or the wait list crossover group (dAPP). Due to the intervention’s nature, this will be a single-blind study in which the results will be assessed blindly but participants will be aware of their group assignment. Participants assigned to fAPP group will use the App initially for 28 consecutive days (T1). During T1, participants assigned to the dAPP group will maintain their usual treatment. After T1, for the next 28 consecutive days (T2), dAPP will use the App and fAPP will maintain the usual treatment, without a wash-out period. We assume that there would be no carry-over effect as the App utilized in this study is not a curative treatment but rather a tool for relieving stress. Therefore, we have decided to use a cross-over design without a wash-out period. Recommendation for Interventional Trials (SPIRIT) flow diagram is presented in Figure 2.

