### 2.7. Interventions

#### 2.7.1. Administration of the App

Participants will be instructed to use the App autonomously for 4 weeks at home, in addition to their usual treatment, during the period of using the App (T1 for fAPP group, T2 for dAPP group). According to their assigned group, each participant will receive basic instructions from the researcher on how to use the App.

As the purpose of using the App is to obtain an additional stress relief effect in the usual treatment for patients with depression, the schedule for the App will not be strictly controlled; the researchers will provide a 4-week schedule as a guideline to ensure the use of more than the minimal. As a minimum standard for usage, the schedule will guide participants to use the components of each module at least once a day, 6 days a week or more, and the use of additional content is left to the participant’s discretion. However, regarding the meditation module, the participants will be guided to conduct training after completing psychoeducation in consideration of the characteristics of the content. The App has implemented a system that alerts the user twice per day at a time they select if it is not utilized at least once per day. The researcher will help participants who have provided permission to activate the alarm system in the App. However, whether a participant follows these guidelines is not a determining factor in excluding respective participants’ data.

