### 2.8. Assessments and outcomes

Assessments will be obtained through the clinician rating scale and self-rating scales during hospital visits. Table 2 presents the schedule for assessments. Assessments conducted at the hospital visits were acquired at the baseline (V_0_) and every 2 weeks (V_1_, V_2_, V3, and V4) during T1 and T2. The baseline assessments will be collected when participants are enrolled and will include their sociodemographic and clinical characteristics. All instruments have been translated to Korean with reliable psychometric properties. The data collection process implanted in the objective monitoring module of the mobile App will be activated through an ID issued after enrollment and randomization.

**TABLE 2 T2:** Schedule for assessments.

Assessments	Baseline	Visit			
		**V1**	**V2**	**V3**	**V4**
Mini international neuropsychiatric interview	V				
Depression, anxiety, and tress scale	V	V	V	V	V
Perceived stress scale	V		V		V
Posttraumatic embitterment disorder scale	V		V		V
Nine-item patient health questionnaire	V	V	V	V	V
Hamilton depression rating scale	V	V	V	V	V
Intervention engagement					V

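### Removal of a participant for clinical risk ends trial assessment as well as App use, which sits badly with the intention-to-treat analysis (minor)

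*Protocol article*

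**What the plan says.** All places are in the protocol article.

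- Section 2.15 (Ethical approval): "the appearance of any important clinical change involving any type of risk would not only imply removal of the participant from the project"; the same sentence adds referral for specialist care. It does not mention further trial assessment.
- Section 2.8 and Table 2: "Assessments will be obtained through the clinician rating scale and self-rating scales during hospital visits". DASS-21, PHQ-9 and HAM-D are taken at baseline and at V1–V4, two weeks apart. Nothing is said about visits after removal.
- Section 2.13: the analysis is "primarily on an intention-to-treat basis". On incomplete follow-up it says: "The first evaluation of participants with missing data will assume that data are missing at random in the linear mixed model". The sensitivity checks are a per-protocol completer analysis, multiple imputation and last observation carried forward.
- Section 2.7.1: "whether a participant follows these guidelines is not a determining factor in excluding" a participant's data. This protects data only where the App-use schedule is not followed.
- Section 2.7.2: "the use of new psychiatric medications, including antidepressants and benzodiazepines, will be limited". A medication change gives the participant the right to withdraw. It does not impose removal.
- Section 2.1: in the second period "dAPP will use the App and fAPP will maintain the usual treatment, without a wash-out period".
- Section 2.14: for a patient who withdraws, the "data will not be used in the analysis and, if desired, will be removed from the project database".

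**The concern.** Stopping an intervention and ending outcome assessment are separate acts, and section 2.15 treats them as one. Its wording takes the participant out of the project, and no other section keeps the remaining visits.

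An intention-to-treat analysis compares the assigned sequences using outcomes from everyone randomized, including those who stop the App. The removal rule withholds some of those outcomes. Where the clinical change is a psychiatric worsening, the missing scores belong to patients selected partly by the outcome. In this crossover, removal during the first period also loses the whole second period, and with it that patient's within-person comparison.

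The planned sensitivity checks do not clearly address this. Multiple imputation as usually run again assumes missing at random. Last observation carried forward repeats a score from before the worsening if the triggering score was not taken. A completer analysis leaves these patients out.

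**Working it through.** **The plan's own figures.** Section 2.12 gives an effect size of 0.28, power 0.95, alpha 0.05, a minimum of 172 and 215 enrolled. A within-patient noncentral t calculation (d = 0.28, two-sided) gives N = 168, with power 0.955 at N = 172. Enrolment is 172 / 0.8 = 215. The sample size is broadly reproduced and is not in dispute. The section does not state the scale of its 0.28; below it is taken in units of the total SD.

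**Visits lost per removed patient** (sections 2.1 and 2.8, four post-baseline DASS-21 scores):
- before V1: 4 of 4
- between V1 and V2: 3 of 4
- between V2 and V3: 2 of 4, which is all of the second period
- between V3 and V4: 1 of 4

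**Simulation inputs.** From the article: five visits, 215 patients (108 and 107), App effect −0.28 in the first period for one sequence and in the second for the other. Assumed: the share removed, the correlation structure and how closely the trigger follows DASS-21.

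- Model for patient i at visit j: y_ij = m_j − 0.28·A_ij + b_i + e_ij, where A_ij is 1 while the App is assigned and the total SD is 1.
- Structure (i): Var(b) = 0.5 with independent residuals. Structure (ii): Var(b) = 0.4 with AR(1) residuals, parameter 0.5.
- Removal occurs at the first visit where a trigger variable has risen from baseline by more than c, with c set to remove 5%, 10% or 15%. The trigger correlates 1 (worst case) or 0.5 with DASS-21.
- Estimate: generalized least squares with visit and App effects; 6000 runs, Monte Carlo SE 0.0006. The SE of the App effect with complete data is about 0.048 (i) and 0.047 (ii).

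**Understatement of the App effect, in SD:**

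| Setting | 5% removed | 10% | 15% |
|---|---|---|---|
| Trigger score recorded and used, (i) and (ii) | within 0.001 | within 0.001 | within 0.001 |
| Not recorded, correlation 1, (i) | 0.012 | 0.021 | 0.029 |
| Not recorded, correlation 1, (ii) | 0.010 | 0.018 | 0.026 |
| The same in standard errors, (i) / (ii) | 0.25 / 0.22 | 0.43 / 0.39 | 0.59 / 0.56 |
| Not recorded, correlation 0.5, (i) / (ii) | 0.003 / 0.002 | 0.005 / 0.006 | 0.007 / 0.006 |

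Relative to 0.28, the worst-case rows run from 0.010 / 0.28 = 3.6% to 0.029 / 0.28 = 10.4%. At correlation 0.5 the understatement is at most 0.14 standard errors. At an assumed 1% and 2% removed (correlation 1, not recorded) it is 0.003 and 0.007 SD, or 0.06 and 0.14 standard errors.

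**No true effect, score not recorded:** bias is within 0.001 SD and two-sided rejection is 3.6–4.4%.

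**If the visits are kept.** Here the App is stopped or not started in every removed patient, and changed treatment lowers later scores by 0 to 0.6 SD. At correlation 1 the estimate falls short of 0.28 by 0.003–0.006 (5%), 0.009–0.013 (10%) and 0.014–0.020 (15%) under (i), and by 0.001–0.003, 0.004–0.008 and 0.009–0.014 under (ii). At correlation 0.5 the shortfall is 0.002–0.019. With no true effect, rejection is 4.3–6.0%; the 6.0% arises at 15% removed with a 0.6 SD treatment change.

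**The case against.** The strongest reply is that this is one general safety sentence in a condensed article, placed just after a statement that no potential risks were found. Procedures after discontinuation usually stand in the full protocol. Part of this holds: the sentence does not say that recorded scores are discarded. But it does state a rule, and the rule is removal from the project. That is a choice the article fixes, not a detail it omits.

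Second, the planned mixed model covers the main scenario. DASS-21 is taken every two weeks, so a worsening found at a visit can be scored there, and the bias is then near zero. Missing later scores also do not in themselves contradict intention to treat. Both points stand, and they are why the concern is minor. The article does not settle whether the triggering score is taken before removal.

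Third, the removal rates are assumed. Entry is limited to HAM-D 7–24 with 28 days of stable medication, and follow-up is eight weeks, so the true rate may be low. This stands too.

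Fourth, the fix shows no reliable gain in accuracy. With a weak link to DASS-21, the kept-score estimate lies no closer to 0.28 than the plan as written. This is correct. What is gained is the effect of the assigned sequence as delivered.

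A reader might also infer that section 2.14 strips removed patients of the scores already recorded. Its wording does not support that: the rule opens with a patient who withdraws, and removal under section 2.15 is decided by the investigators.

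**Conclusion.** The concern holds as a minor design point. Section 2.15 ends trial participation where stopping the App would be enough, and the lost scores can be related to the outcome.

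Bias is near zero if the triggering score is recorded and used under missing at random. Otherwise the App effect is understated by at most about 0.03 SD (0.6 standard errors), at an assumed 15% removed and with removal driven wholly by the analysed score. The sizes rest on assumed removal rates, the two assumed correlation structures and reading 0.28 on the total-SD scale.

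Two stronger readings are not supported. One is that the rule favours the App or produces false positives: the simulated bias is toward no effect, and rejection under no effect stays below 5% with the plan as written. The other is that every removal is tied to the outcome: the trigger covers any type of risk, so it may be physical and unrelated to DASS-21.

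**What to change.** Reword section 2.15 so that an important clinical change involving risk leads to referral and, where clinically indicated, to stopping or not starting the App. The V1–V4 assessments already scheduled should continue unless the participant withdraws consent to them. Analyse those scores, and all scores already recorded, in the assigned sequence. The clinical criteria stay with the investigators.

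A sentence in section 2.14 that its rule on withdrawn patients' data does not apply to removal by the investigators would be a useful clarification. It is not part of the defect.

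The cost is protocol wording and a short site instruction, with no extra visits or patients. The downside is that some kept scores will reflect changed treatment, which section 2.7.2 tries to limit. Without a wash-out, treatment started in the first period can carry into the second. The intention-to-treat estimate includes those changes, and the report should say so.
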